### Withdrawal and Crisis Management Procedure

Participants can withdraw from the RCT at any time without penalty and are not required to provide reasons for their decision. In terms of crisis management, emergency psychiatric services will be available at UPM Teaching Hospital to assist participants in cases of crisis or distress that exacerbate their symptoms or lead to significant deterioration in functioning. All clinic attendees will have access to this service. The investigators will be notified if any medical student utilizes the emergency service, at which point a decision will be made regarding the RCT and whether the crisis qualifies as an adverse event related to the trial.

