### Blinding

Single blinding will be implemented in this trial. As an online self-report assessment will be conducted, the researchers will remain blinded to the outcomes during the RCT. An automated email will inform the participants of the randomization results, so the medical students will know which group they are assigned to. Limited contact will be maintained between the researchers and participants to prevent any bias in the allocation process or influence on the subsequent assessments. The assessors will remain blinded even after participants contact the research team and reveal their allocation. A researcher (VM; University Putra Malaysia), who has access to all data, will perform the statistical analyses.

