Besides the overall recommendations on sleep hygiene, the medical students will be encouraged to focus on specific behaviors that received the highest scores in the Sleep Hygiene Index (SHI; ie, reducing coffee or alcohol consumption just before bedtime if the participant reports frequent use). They will also be guided by the Dysfunctional Beliefs and Attitudes About Sleep-16 (DBAS-16), particularly for participants who score highly on the item “feel irritable, depressed, or anxious during the day, mostly because I did not sleep well the night before.” This reflects a strong belief in the negative impacts of poor SQ. Such participants will be advised to explore whether there are any underlying reasons for their anxiety and depression, aside from insomnia.

The internet program will serve as the primary medium for delivering all intervention materials, with participants engaging with the materials independently. They will also have the opportunity to consult a clinical psychologist (see the “Withdrawal and Crisis Management Procedure” section). Additionally, participants are strongly encouraged to use the feedback form to contact a specialist, particularly if they are newly recruited into the RCT, experiencing negative effects from the ICBT-I or ISHE interventions, or encountering methodological or technical difficulties with the program. The content of the intervention is entirely based on the well-established ICBT-I, which has been validated and tested in previous studies [37].

Each module will be completed with a homework report, which participants will fill out and submit to their therapists. The therapist will review the report, worksheets, and sleep diary data. Written feedback will be provided within 48 hours, and the therapist will grant the medical student access to the subsequent module. Meanwhile, if the participant is inactive for 1 week, the therapist will be alerted via a mobile phone SMS text message, serving as a reminder and encouragement. If necessary, another SMS text message will be sent, followed by emails, with phone calls as the final step. The therapist (FM) in this study is a licensed clinical psychologist with expertise in poor SQ and insomnia-related CBT.

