### Assessment of Participants’ Safety

The risk of severe or serious adverse events in this study is low, as no such events have been reported in previous studies using CBT-I for the management of insomnia [49].

Nevertheless, studies have shown that sleep restriction therapy, one of the components of CBT-I, may increase levels of vigilance impairment and daytime sleepiness among participants, potentially leading to adverse situations such as suicide attempts, incidents, and formal complaints about the online intervention [49]. As both the intervention and assessment will be conducted online, the researcher may not be made aware of all such events. The researcher will, however, instruct participants to complete a feedback form to report any self-reported adverse effects [50].

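### The crisis procedure settles adverse-event status and trial-relatedness in one decision, without providing that unrelated crises are still recorded by arm or that those deciding are blind to arm

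*Protocol article*

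**What the plan says.** The rule is in Methods, Withdrawal and Crisis Management Procedure. Notification comes first: "The investigators will be notified if any medical student utilizes the emergency service". The classification step follows: "at which point a decision will be made regarding the RCT and whether the crisis qualifies as an adverse event related to the trial". The section gives no criteria, does not say who decides, and does not say what happens to a crisis judged unrelated.

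Four other parts of the article bear on this:

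- **Assessment of Participants' Safety** calls the risk of serious events low. It then names sleep restriction as a possible source of impaired vigilance and daytime sleepiness, "potentially leading to adverse situations such as suicide attempts, incidents, and formal complaints about the online intervention". It adds a second reporting route, under which the researcher will "instruct participants to complete a feedback form to report any self-reported adverse effects", and concedes that "the researcher may not be made aware of all such events".
- **Blinding** describes a single-blind trial in which participants know their group. Of the researchers it says "the researchers will remain blinded to the outcomes during the RCT". Of the assessors it says "The assessors will remain blinded even after participants contact the research team and reveal their allocation".
- **The Internet Group (CBT-I)** has the therapist review each module's homework and diary data and release the next module. On support it says "They will also have the opportunity to consult a clinical psychologist" and refers the reader to the crisis section for details.
- **The Internet-Based SHE** states that the comparator contains no sleep restriction.

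**The concern.** Whether an untoward event happened and whether the intervention caused it are separate questions. The first is a matter of record. The second is a judgement, usually an uncertain one, and it is open to the expectations of whoever makes it. If the first is made to depend on the second, an event thought to be unrelated may never reach the table, and a reader cannot tell that it occurred.

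In a two-arm trial the comparison of all events by arm is what guards against misattribution, because unrelated events should fall about equally in both arms. Filtering by perceived cause before counting gives up that protection. It matters most when those judging may know the arm and hold a causal theory that points to one arm. Suicide attempts are the gravest event the article names. In a trial of this size, one or two classifications can decide whether the report says that no adverse events occurred.

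**Working it through.** The article states no adverse-event rate, count or safety threshold, so there is no figure to reproduce. The check is a reading of the relevant sections together, followed by one illustration of scale.

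**Step 1. What is being decided?** The crisis section asks whether the crisis qualifies as an adverse event that is related to the trial. The grammar allows two readings:

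- (a) Status and relatedness are one test, so a crisis judged unrelated does not qualify.
- (b) The event is recorded in any case and the decision is an ordinary causality assessment.

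Reading (a) is the more natural, but nothing in the section excludes (b). Nor does any sentence say that a crisis judged unrelated is kept on record by arm.

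**Step 2. Does the other reporting route close the gap?** The feedback form carries no relatedness condition, so it could catch some of the same events. It relies on the student reporting, however, and the same section concedes that events may be missed. It also does not say how a crisis notified through the emergency service is classified, which is the question here.

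**Step 3. Are those deciding blind to arm?** The article does not say.

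- Researchers are described as blind to outcomes, which is not blindness to allocation.
- Assessors are described as blind, but nothing says that they judge crises.
- The therapist reviews arm-specific homework and so must know the arm. By the initials given, the therapist is also the psychologist who supervises data collection (Data Collection Procedures). The article does not say that the therapist makes the crisis decision.

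**Step 4. Could judgement lean by arm?** The only cause of harm named in the safety section is sleep restriction, which ICBT-I contains and ISHE does not. A judge who knows the arm therefore has a stated reason to call a crisis related in one arm and no matching reason in the other. Against this, the ICBT-I section invites feedback from anyone with negative effects of either intervention, so harm in the ISHE arm is not ruled out.

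**Step 5. Scale, as illustration only.** Inputs: n = 60 per arm (Sample Size Estimation; Randomization and Allocation Concealment). Assumption: one crisis occurs in an arm. The exact (Clopper-Pearson) one-sided 95% upper limit p for x events solves P(X ≤ x | n, p) = 0.05.

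- x = 0: (1 − p)^60 = 0.05, so p = 1 − 0.05^(1/60) = 4.9%.
- x = 1: (1 − p)^60 + 60p(1 − p)^59 = 0.05, so p = 7.7%.

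Leaving out that one crisis turns 1/60 into 0/60 and lowers the upper limit from 7.7% to 4.9%. At the hypothetical extreme, with 3 crises in each arm, calling all of those in ICBT-I related and none of those in ISHE related would turn 3 v 3 into 3 v 0. That bounds what attribution could do with those counts; it is not a forecast.

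**Step 6. The cross-reference.** The ICBT-I section sends the reader to the crisis section for the psychologist consultation. The crisis section describes withdrawal and the emergency service and mentions no such consultation. The two do not match.

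**The case against.** The strongest answer is that the sentence is loosely worded rather than wrong. It can describe a causality assessment of an event already notified. The article states no rule that discards unrelated crises and defines no adverse-event count from which they could be taken. Being a condensed account, it would commonly leave event definitions, forms and adjudication to the full protocol. The stated risk of serious events is low, and students with suicidal intentions are excluded.

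Most of this stands, and it limits the point. A reader might infer that harms will be removed from the count by people who know the arm. The article does not support that: removal is not stated, the decision-maker is not named, and assessors are said to stay blinded. A reader might also infer that attribution will necessarily differ by arm. That does not follow either, because negative effects are anticipated under both interventions. The decision about the RCT might be taken to mean the fate of the whole trial, but under a withdrawal heading it may mean only that student's participation.

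Nor does the unmatched cross-reference show that a distressed student has no help short of the emergency service. The ICBT-I section itself provides a feedback form for reaching a specialist, and written therapist feedback within 48 hours.

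What the objection does not remove is the wording. The article chose to state a classification rule, and that rule joins occurrence to attribution. The condensed format excuses silence, but this is a stated rule that can be read as conditioning the record on relatedness.

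**Conclusion.** The point holds in a limited form. The crisis section merges adverse-event status with relatedness in one decision. It does not secure that unrelated crises are recorded by arm, and it does not require those deciding to be blind to arm. Together with researcher blinding that covers outcomes only, a therapist who must know the arm, and a single named cause of harm confined to ICBT-I, this means the harms report could be filtered by perceived relatedness. That is a risk left open by the wording, not a bias shown to be present.

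Its size cannot be estimated, because the article gives no crisis rate. The limits of 4.9% and 7.7% assume 60 per arm and a single crisis, and show only that one classification alters the safety statement. The conclusion rests on the article alone; if the full protocol already records all crises by arm, the remedy is to make the article's sentence agree with it.

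The change is worth making because it is cheap and the events are grave. The cross-reference is a minor editorial matter.

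**What to change.** Reword Withdrawal and Crisis Management Procedure to provide that:

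1. Every known use of the emergency service, suicide attempt or other crisis from randomisation to T4 is recorded and reported by arm as an adverse event, whatever its cause.
2. Relatedness is a separate field and never decides whether an event is counted. It is first rated on a case summary with the arm masked, by an existing investigator who is not the therapist.
3. The report shows all events and related events side by side, by arm.

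Separately, reconcile the reference to a psychologist consultation in The Internet Group (CBT-I) with the crisis section, either by describing the consultation there or by correcting the reference.

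The cost is protocol wording, one field on the event form and a short masked summary per event. The drawback is that a few unrelated events will appear in the table. The article schedules T3 and T4 for completion by July 2025 and the analysis for August 2025. On that timetable the rule can govern later events, and it can be applied to earlier ones if their notifications were kept.

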### Data Collection Procedures

The primary researcher (VM) will collect all data under the supervision of a registered and licensed clinical psychologist (FM). The researcher holds a master’s degree in clinical psychology and meets the minimum qualifications to administer all questionnaires to participants. Online assessments will be conducted by the clinical psychologist, using an instrument with Yes or No responses to items related to the inclusion and exclusion criteria. All clinical interviews will be audio-recorded to enable subsequent reliability assessments (see Multimedia Appendices 3 and 4 for the study information sheet and consent form, respectively). Participants who are willing to participate will be provided with a consent form. Their consent will be confirmed once they sign the form. Participants who meet the inclusion criteria and have PSQI scores greater than 5 will be grouped and asked to complete the online Trail Making Test, DBAS-16, PSAS, and SHI.

### Monitoring of Intervention and Follow-Up Assessment

The flowchart for the research activities is summarized in Figure 2. An SMS text message reminder will be sent by the Zoom administrator 1 day prior to and 30 minutes before the intervention. Follow-up assessments will be conducted at 1-month, 3-month, and 6-month intervals after the postintervention to reassess participants’ SQ, executive functioning, self-reported sleep problems, SE, sleep cognition, and presleep arousal. The same instruments described in the previous section will be used for the assessments. All participants will be monitored for adherence to the intervention, and potential dropouts will be identified and addressed accordingly.

### Data Analysis

Data will be analyzed using SPSS version 29 (IBM Corp.). Descriptive statistics will be used to obtain information on dropout rates, recruitment, and completeness. All participants will be included in the intention-to-treat analysis for assessing the main efficacy of the intervention, with no planned interim analysis for efficacy or futility. The baseline characteristics of participants will be presented according to their randomized group, with no inferential statistical tests performed at this stage.

For the RCT design, outcome measures will be assessed for normality and presented as either means with SD or medians with IQR, depending on the data distribution. Participants’ characteristics will be summarized using descriptive statistics, with categorical data presented as frequencies and percentages, and continuous data presented as means (SD) or medians (IQR). Normality will be tested using the Kolmogorov-Smirnov and Shapiro-Wilk tests.

Changes in all outcome measures (ie, SOL, TST, NOA, WASO, SQ, SE, dysfunctional beliefs about sleep, presleep arousal, and SHI) from pretreatment (T0) to the first (T1), second (T2), and third (T3) time points will be assessed for treatment effects using repeated measures analysis of variance. Both treatment and time interaction effects will be examined. Paired samples *t* tests will then be conducted within each condition to evaluate possible simple or main effects. Significant findings and statistical trends will be further analyzed using Cohen *d* effect size, which accounts for the correlation between pre- and posttreatment values.

Potential confounding factors, particularly class year and gender, will be addressed and analyzed as variables that may influence the research outcomes. These factors will be incorporated into the analysis through both univariate and multivariate linear regression analyses, allowing for the isolation of each factor and its association with the outcomes of interest.

Regarding the fourth hypothesis, mediation analyses will be conducted to explore whether changes in the outcome measures from pretreatment to posttreatment are significantly mediated by dysfunctional beliefs and attitudes about sleep, sleep hygiene, and presleep worry. The analysis will follow the traditional mediation model, where the direct, indirect, and total effects are defined in terms of the linear regression coefficients [51]. For example, when the mediation effect size is medium (ie, SM) and the intraclass correlation coefficient is 0.2, with 4 repeated measures, the Sobel method would require 191 participants to achieve 80% power. By contrast, the product-of-coefficients and bootstrap methods would require 188 and 185 participants, respectively, to achieve the same power [52]. This study will adopt the bootstrap method for mediation analysis due to its flexibility in terms of sample size requirements.

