**Methods:**

A parallel group, RCT with a target sample of 120 medical students recruited from government-based medical universities in Malaysia. Eligible participants will be randomized to internet group CBT-I or internet group SHE in a 1:1 ratio. Assessments will be performed at baseline, post-intervention, 1 month, 3-months, and 6-months. The primary outcome is between-group differences in sleep quality and executive function post-baseline. The secondary outcomes include pre-sleep worry, attitude about sleep, sleep hygiene and sleep parameters.

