### Research Aim and Hypotheses

This study aims to elucidate the effects of improved SQ on executive function. The following hypotheses will be investigated in the trial:

ICBT-I will lead to a significant improvement in SQ compared with the SHE intervention at 1 month (T2), 3 months (T3), and 6 months (T4) postintervention.ICBT-I will lead to a significant improvement in executive functioning compared with the SHE intervention at 1 month (T2), 3 months (T3), and 6 months (T4) postintervention.ICBT-I will lead to a significant improvement in total sleep time (TST), SOL, number of awakenings (NOA), wake time after sleep onset (WASO), and sleep efficiency (SE) compared with the SHE intervention at 1 month (T2), 3 months (T3), and 6 months (T4) postintervention.Dysfunctional beliefs, attitudes about sleep, presleep worry, and sleep hygiene will significantly mediate the between-group differences in study outcomes at 1 month (T2), 3 months (T3), and 6 months (T4) postintervention.

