### Assessment Points

Participants in both groups will be assessed at baseline (week 0 or pretreatment assessment), week 6, 1 month, 3 months, and 6 months after the intervention. T0 represents the pretreatment assessment, while the subsequent 4 assessment points are designated as T1, T2, T3, and T4, respectively.

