#### Digital Trail Making Test

Executive functioning will be assessed using a self-reported online version of the dTMT, which includes TMT-A and TMT-B. In TMT-A, participants are required to connect a sequence of numbers in order. In TMT-B, participants must alternately connect numbers enclosed in circles and squares, following the sequence while ensuring that the pen remains in contact with the paper throughout the process. Participants’ executive functioning will be evaluated based on the time taken to complete the entire test and the accuracy of the number connections [40].

In this study, the dTMT will be used to assess medical students’ executive functioning. The TMTs are widely used in neuropsychological assessments due to their sensitivity to various neurological disorders. The test consists of 2 conditions (A and B) [41]. In part A, medical students will be instructed to draw a line sequentially connecting a total of 26 numbered circles as quickly as possible. In part B, each student will be asked to connect a series of 26 circles containing either a number or a letter, alternating between them. Both conditions will be scored based on the total time taken to complete the tasks and the frequency of errors made.

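### The treatment-effect analysis omits executive function, a primary outcome, and stops at T3, although the hypotheses claim effects at 6 months; the mediation window has a similar mismatch

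*Protocol article*

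**What the plan says.** **Primary outcome.** The Methods paragraph of the Abstract states: "The primary outcome is between-group differences in sleep quality and executive function post-baseline".

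**Hypotheses.** Under Research Aim and Hypotheses, hypothesis 1 predicts a "significant improvement in SQ compared with the SHE intervention at 1 month (T2), 3 months (T3), and 6 months (T4"), and hypothesis 2 a "significant improvement in executive functioning compared with the SHE intervention at 1 month (T2), 3 months (T3), and 6 months (T4"). Hypothesis 3 makes the same claim for five sleep parameters. Hypothesis 4 claims mediation of the between-group differences at the same three visits.

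**Schedule.** After baseline (T0), Assessment Points says that "the subsequent 4 assessment points are designated as T1, T2, T3, and T4, respectively"; these are week 6 and then 1, 3 and 6 months. Monitoring of Intervention and Follow-Up Assessment lists executive functioning among the things reassessed at 1, 3 and 6 months. Results says T3 and T4 will be complete by July 2025, with analysis to be finished by August 2025.

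**Treatment-effect analysis.** Data Analysis specifies repeated measures ANOVA for "Changes in all outcome measures (ie, SOL, TST, NOA, WASO, SQ, SE, dysfunctional beliefs about sleep, presleep arousal, and SHI"), from T0 "to the first (T1), second (T2), and third (T3) time points will be assessed for treatment effects". Paired t tests within each arm follow.

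**Mediation.** The last paragraph of Data Analysis examines change from pretreatment to posttreatment.

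**The concern.** The ANOVA sentence is the only place where the article assigns outcomes and visits to a test of treatment effect. It disagrees with the rest of the article twice: a primary outcome is missing from its outcome list, and the last follow-up is missing from its visits. An analyst who followed it literally would produce no between-group result for executive function at any visit, and none for any outcome at 6 months. The mediation results would likewise not address the visits named in hypothesis 4.

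If the gap is filled late, choices about a primary outcome could be made with results in view. The Digital Trail Making Test section scores two parts on time and on errors, which gives four candidate scores. Results reports T1 and T2 data complete for all enrolled participants, and Blinding says the researcher who will run the statistics has access to all data.

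**Working it through.** This is mainly a comparison of text. A short calculation then checks whether the fix affects sample size.

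**1. Outcomes.** The ANOVA list has nine entries: SOL, TST, NOA, WASO, SQ, SE, dysfunctional beliefs, presleep arousal and SHI. Of the two primary outcomes, sleep quality is listed; executive function and the dTMT are not. The list is introduced by *ie* (that is), so in form it defines the set rather than giving examples.

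**2. Visits.**

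| Visit | Scheduled | Named in hypotheses 1–3 | In the ANOVA sentence |
|---|---|---|---|
| T1 (week 6) | yes | no | yes |
| T2 (1 month) | yes | yes | yes |
| T3 (3 months) | yes | yes | yes |
| T4 (6 months) | yes | yes | **no** |

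The hypotheses tie T3 to 3 months and T4 to 6 months, and the ANOVA sentence uses the same labels. A different numbering therefore does not explain the gap. One of four post-baseline visits is missing.

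**3. Could another analysis fill the gap?**
- The regression paragraph deals with class year and gender as confounders. It names neither executive function nor a visit and describes no comparison of arms.
- The paired t tests are within arm.
- The mediation paragraph refers only generally to the outcome measures and to pretreatment-to-posttreatment change. It names no follow-up visit, whereas hypothesis 4 names T2, T3 and T4.

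None of them assigns executive function or T4 to a between-group test.

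**4. Does adding T4 need more participants?** Inputs from Sample Size Estimation: within-between interaction, f = 0.20, correlation 0.5, alpha 0.05, power 0.95, two groups. Sphericity is assumed (epsilon = 1). The number of measurements m is not in the text. For total sample size N:

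λ = N·m·f²/(1 − ρ), df1 = m − 1, df2 = (N − 2)(m − 1)

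- m = 4, N = 56: λ = 56 × 4 × 0.04/0.5 = 17.92, df 3 and 162, power 0.954.
- m = 5, N = 48: λ = 48 × 5 × 0.04/0.5 = 19.2, df 4 and 184, power 0.952.
- N = 120: λ = 38.4 (m = 4) or 48.0 (m = 5), power above 0.999 in both cases.

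The article's figure of 56 per group is not reproduced as a per-group number; 56 is the total at m = 4. That is a separate matter. It is consistent with planning on T0 to T3, but this is an inference. What matters here is that, on the article's own test, moving from m = 4 to m = 5 lowers the required total from 56 to 48, so adding T4 does not call for a larger sample.

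**The case against.** The strongest reply is that this is a slip, not a decision. The governing phrase covers all outcome measures, the dTMT is described under the Outcome Measures heading, the same instruments are to be used at every follow-up, and analysis is scheduled after T4 has been collected. All of this suggests that the authors meant to analyse both. That is plausible. It counts against any charge that the trial has chosen not to test hypothesis 2, but it leaves the contradiction in place. Nor is this detail that an article may leave to an analysis plan, because the article states the outcome list and the visits explicitly. A plan that copied the sentence would drop a primary outcome; one that departed from it would contradict the published protocol.

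On mediation, posttreatment could loosely include the follow-ups. The text does not say so, and the Abstract lists the post-intervention assessment separately from the 1-, 3- and 6-month ones.

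A reader might go further in three ways that the document does not support:

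- *That analysing T1 is an error because no hypothesis names it.* The Abstract defines the primary outcome as post-baseline and lists a post-intervention assessment, so T1 falls within it.
- *That a definite fraction of primary contrasts is covered, such as sleep quality at T2 and T3 out of two outcomes at three visits.* The plan describes an interaction test and within-arm t tests. It never sets out between-group contrasts visit by visit, so such a count has no basis.
- *That the choice of dTMT score, or the description of part B, is itself the defect.* An endpoint score is commonly fixed in a fuller document. The part B mismatch is real: "participants must alternately connect numbers enclosed in circles and squares" in one paragraph, circles with numbers or letters in the next. But it concerns the instrument, not whether a test is planned. Both are worth settling in the same amendment.

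**Conclusion.** The point holds as an internal contradiction. Taken as written, Data Analysis gives one of two primary outcomes, and one of four post-baseline visits, no stated between-group test. The mediation window does not match hypothesis 4. This rests on reading the *ie* list as closed and on no other part of the article supplying the missing test; I found none that does.

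It would be too strong to say that the trial will never test executive function or 6-month durability, since the data are to be collected and the authors may well intend to analyse them. The document also does not say whether anyone has looked at outcome data by arm, so no selective analysis can be inferred; the risk is only that the text leaves room for it. The correction matters because a primary outcome is affected, and it is cheap. The sample-size remark assumes sphericity and the same effect size, 0.20, for the dTMT, and concerns the overall interaction test only.

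**What to change.** Issue one dated amendment before outcome data by arm are examined, and state in it that they have not been. It should:

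1. Add executive function (dTMT) to the outcomes in the repeated measures sentence.
2. Extend the visits in that sentence to T0 through T4.
3. Align the mediation window with hypothesis 4 (T2 to T4).
4. State which dTMT score is the executive-function endpoint. The choice is the sponsor's; nothing in the article favours one.
5. Reconcile the two part B descriptions, so that the version actually administered is the one described.

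**Cost.** A little more analysis work, and a documented amendment that comes after T1 and T2 data have been collected, which should be acknowledged openly. No new data collection is needed, because the dTMT and the T4 visit are already in the schedule. On the article's own sample-size test, adding T4 does not require more participants.
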